### Data collection

At the start of the study (t = 1), GPs in the intervention group were asked to use RADPAC to screen the medical records of all patients in their practice to identify patients with COPD, CHF or cancer who potentially could benefit from a palliative care approach. They were instructed to continue to use RADPAC each time new data of a patient with CHF, COPD or progressive cancer was available. In 2011, anonymous data were collected retrospectively from the medical records of all patients that had a non-acute death during the intervention period, as well in the intervention as in the control practices (t = 2). All deceased patients who were diagnosed with CHF, COPD and/or cancer were included (Figure 2). Each non-planned (out of hour) contact and hospital or nursing home admission during the study was derived from the medical record and registered as well as place of death and if the patient had been identified as being in the palliative trajectory. Besides, qualitative data were collected concerning proactive care planning in both study groups.

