### Participants

GPs in two comprehensive cancer centre (IKO and IKZ) regions in the South-East of the Netherlands were invited by mail to participate in the study. After one month a reminder was send to non-responders. Excluded were GPs who are consultant in palliative care or who are locum. GPs that wanted to participate were stratified for degree of urbanization and working hours (part-time or full-time) and were randomized assigned to the intervention or the control condition by an independent statistician. To prevent contamination, those GPs working together in the same practice were placed in the same study group.

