### Outcomes

GPs of both study groups were invited to extract data of all patients that died during the observational period from the medical records: demographics, disease history, place of death, hospital admissions and out of hours consultations. Of each participating GP, demographic characteristics, practice characteristics and their interest in palliative care were collected (Table 3).

**Table 3 T3:** Baseline characteristics participating GPs^# ^(n = 133)

*Characteristics of general practitioners *	
Age - yr	48,2 ± 8,1

Gender male sex - no.(%)	81 (60, 9)

Working week fulltime - no. (%)	70 (52, 6)

Experience - no. (%)	

≤ 1 year	2 (1, 5)

2 - 5 years	14 (10, 5)

6 - 10 years	21 (15, 8)

≥ 10 years	94 (70, 7)

Missing	2 (1, 5)

Interest in palliative care*	8, 14 ± 1, 12

Missing	3

Estimation of own capability**	6, 83 ± 0, 92

Missing	3

*Characteristics of practice *	

Practice form - no. (%)	

Single-handed	28 (21, 1)

Dual	53 (39, 8)

Group and health centres	52 (39, 1)

Missing	0

Degree of urbanisation - no. (%)	

Very	46 (34, 6)

Moderate	28 (21, 1)

Less	41 (30, 8)

No	18 (13, 5)

Missing	0

Size of practice Fte-average practice^+^	1728 ± 409

Missing	1

*Palliative care*	

Palliative patients/y - no. (%)	

≤ 2 patients	10 (7, 5)

3 - 5 patients	72 (54, 1)

5 - 9 patients	43 (32, 3)

≥ 10 patients	6 (4, 5)

Missing	2 (1, 5)

Use of consultant palliative care - no. (%)	

Yes	105 (78, 9)

No	25 (18, 8)

Missing	3 (2, 3)

^#^Plus-minus values are means ± SD

^+ ^Size of practice = fulltime-equivalent/average practice (= 2350 patients)

*Interest in palliative care, visual analogue scale, rang 0, indicating no interest, to 10 very much interest.

** Estimation of own capability, visual analogue scale, rang 0, indicating not capable, to 10 very much capable.

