### Data management and plan of statistical analysis

All data were entered in a database and analysed with SPSS 16.0. In both study groups, all patients who died during the inclusion and observation period of the study of a non-acute death, were included in the retrospective analysis. Intervention and control group will be compared on the main outcomes (place of death, number of transitions and out of hours contact, amount of identified patients). Recruitment rates and drop-out rates will be calculated. In case denominators prove to be significantly correlated with the outcome of the main study question, an Anova will be performed to identify potential related or independent factors. Multilevel analysis will be performed.

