### Weaknesses

Those GPs that were interested to take part in the study, probably have a special interest in palliative care. Besides, as there is a lot of attention for proactive palliative care in medical journals and in Dutch policy, GPs in the control group might be influenced by new information or followed courses. This implies that it might be difficult to find significant differences between intervention and control group. As patients were identified by their own GP, we were not able to influence this process directly.

We did not choose to collect prospective patient data in the control group, as this would be a sort of intervention. Therefore, effect measurement took place retrospectively. GPs in both intervention and control group were asked to collect retrospective data from their digital patient information system. This implies that we do not have patient data of non-responding GPs.

We performed a multifaceted intervention: a combination of training GPs and offering them tools to facilitate early identification and proactive care planning. Usually, multifaceted interventions are more effective than single interventions,[36] but the relative impact of each component of the intervention cannot be established.

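### The analysis set is limited to non-acute deaths, a feature fixed after randomisation and under no stated rule, so selection alone could separate the arms, in either direction

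*Protocol article*

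**What the plan says.** Under Participants, the GPs who agreed to take part "were randomized assigned to the intervention or the control condition by an independent statistician". The patients analysed are found later. Under Data collection, "anonymous data were collected retrospectively from the medical records of all patients that had a non-acute death during the intervention period", in intervention and control practices alike. The next sentence adds the disease criterion: "All deceased patients who were diagnosed with CHF, COPD and/or cancer were included". The analysis section keeps the restriction, taking in "all patients who died during the inclusion and observation period of the study of a non-acute death", without repeating the diagnoses. The Outcomes section describes a wider collection: "GPs of both study groups were invited to extract data of all patients that died during the observational period".

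On who handles the records, the Weaknesses section says that "GPs in both intervention and control group were asked to collect retrospective data from their digital patient information system". The intervention section states that intervention GPs were trained in early identification and in predicting how patients would deteriorate and die. The Control group section states that control GPs received no training and neither tool. The article gives no definition of a non-acute death, names no one who classifies deaths, and does not mention blinding.

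**The concern.** Randomisation makes the two groups of GPs comparable. It protects a comparison of their patients only if patients enter the analysis in the same way in both arms. Here entry depends on a feature of the death, settled after allocation. Whether a death looks acute depends partly on whether it was foreseen, and foreseeing it is what one arm was trained to do. The same death might therefore be counted in one arm and left out in the other.

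The filter is also unlikely to be neutral for the outcomes. Unexpected deaths plausibly differ from expected ones in place of death, admissions and out-of-hours contacts, the three measures named in the study hypothesis. If the arms apply the filter differently, these measures can differ with no effect of the training, or a real effect can be masked. The number of identified patients, which the analysis section also lists as a main outcome, is drawn from the same filtered set.

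**Working it through.** **The plan's own figure.** The only design figure is 96 patients per group, for a 20% reduction in out-of-hours contacts with 80% power and alpha 0.05. It cannot be reproduced from the article alone, because no baseline rate, mean or SD is given. It is attainable: a two-sided test of 55% against 35% with pooled variance gives 96. The point here does not depend on it; 96 serves below only as the number per arm.

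**Inputs.** The article gives no share of acute deaths, no home-death rate and no classification rates. Every input below is an assumption, and the treatment effect is set to zero throughout.

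**1. Extreme case.** Let p be the true home-death share in both arms. One arm drops a fraction f of its non-home deaths as acute; the other drops none. The arm that drops them shows

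p / [p + (1 − p)(1 − f)]

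- p = 0.5, f = 0.1: 0.5 / (0.5 + 0.45) = 52.6%
- p = 0.5, f = 0.2: 0.5 / (0.5 + 0.40) = 55.6%
- p = 0.5, f = 0.3: 0.5 / (0.5 + 0.35) = 58.8%
- p = 0.4, same f: 0.4/0.94 = 42.6%, 0.4/0.88 = 45.5%, 0.4/0.82 = 48.8%

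The formula does not say which arm this is. If intervention GPs drop more deaths, it is a false benefit. If training makes more deaths look expected, control GPs drop more, the control arm is inflated, and a benefit is hidden.

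**2. Softer case, home death.** Let a share b of deaths be borderline between acute and non-acute. An arm includes borderline deaths with probability q and all other deaths with certainty. Home death is x among borderline deaths and 50% among the rest. The observed share is

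[b·q·x + (1 − b)·0.5] / [b·q + (1 − b)]

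with b from 0.1 to 0.3 and x from 0.1 to 0.3.

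- Equal q in both arms: difference 0.
- q = 0.5 control, 0.9 intervention: the intervention arm is lower by 0.8 to 4.1 points. Smallest case (b = 0.1, x = 0.3): 0.465/0.95 = 48.95% against 0.477/0.99 = 48.18%.
- q = 0.2 control, 0.9 intervention: lower by 1.4 to 8.0 points. Largest case (b = 0.3, x = 0.1): 0.356/0.76 = 46.84% against 0.377/0.97 = 38.87%.
- Swapping q between the arms reverses the sign and leaves the size unchanged.

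With 96 independent patients per arm and a two-sided 5% z-test, the null is rejected in 5.1% to 8.9% of trials for 0.5 against 0.9, and in 5.4% to 20.2% for 0.2 against 0.9. Clustering by GP is ignored here.

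**3. Softer case, out-of-hours contacts.** Let borderline deaths have r times the mean contacts of other deaths, with r from 0.25 to 3. Each arm's mean, relative to that of other deaths, is [b·q·r + (1 − b)] / [b·q + (1 − b)]. The intervention/control ratio is

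- 0.91 to 1.15 for q = 0.5 control, 0.9 intervention;
- 0.84 to 1.34 for q = 0.2 control, 0.9 intervention. With b = 0.3: r = 0.25 gives 0.791/0.941 = 0.84, and r = 3 gives 1.557/1.158 = 1.34.

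The design effect is a ratio of 0.80, if the 20% reduction is read as relative.

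**The case against.** The strongest reply has four parts.

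- **The filter is the same in both arms and suits the question.** Proactive planning can do little for a truly sudden death. This stands as a reason to keep a non-acute analysis. It does not make that set safe as the only one, because the same words need not be applied in the same way.
- **The article does not say that GPs, knowing their arm, label the deaths.** A reader might infer this, but the text says only that GPs extract the data. The training concerned living patients at identification, not the labelling of past deaths. The full protocol may also hold a definition. All of this stands, and differential classification is therefore a plausible risk rather than a stated fact. A definition would narrow discretion, but selection would still follow randomisation.
- **The sections need not contradict each other.** A reader might see three rival analysis sets. The diagnosis sentence under Data collection can be read as narrowing the sentence before it, and GPs may extract more than is analysed. This largely stands. What remains is that Outcomes has all deaths extracted, Data collection has non-acute deaths collected, and the analysis section restricts to non-acute deaths without naming the diagnoses, so the set is left unclear.
- **The bias is modest unless classification differs sharply.** This stands, as the softer case shows.

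The Weaknesses section acknowledges retrospective collection and missing data from non-responding GPs, but not selection of deaths by arm.

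**Conclusion.** The point holds as a risk that the stated design creates, not as a demonstrated bias. The set is restricted on a post-randomisation feature, no rule or classifier is stated, and one arm was trained in a skill that bears on that feature. The spurious home-death difference would be about 1 to 8 points under the softer assumptions, and 2.6 to 8.8 points (52.6 − 50 and 58.8 − 50) in the extreme case from a 50% base. These sizes rest wholly on assumed inputs.

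A reader might infer that the filter favours the training. The documents do not support that. If training makes more deaths look expected, control GPs would exclude more of them; where those are mostly non-home deaths, the training would look worse on place of death than it is. For contacts the direction depends also on whether borderline deaths have more or fewer contacts than others. Because every main outcome uses this set, it should be settled before the arms are compared.

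**What to change.** - **Main set:** all deaths, acute or not, in both arms, among patients with a diagnosis of CHF, COPD or cancer, within one common window. The sections name the window differently (intervention period, observational period, inclusion and observation period), so use one term with dates.
- **Sensitivity set:** non-acute deaths under one written rule applied identically in both arms, preferably by someone unaware of the arm. The rule should not depend on whether the GP had foreseen the death or identified the patient as palliative.
- **Further sensitivity analysis:** only patients whose diagnosis was recorded before the start date.
- **Check on selection:** deaths included and excluded by arm, per 1000 listed patients. Practice size is already collected (Table 3).

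The analysis section still puts the comparison in the future tense, so the set can be fixed first. If all deaths were extracted, as the Outcomes section describes, the cost is rewording and a few extra tables. If only non-acute deaths were collected, the remaining deaths must be extracted from the practices.

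There are two further costs. Truly sudden deaths will dilute the effect somewhat. The main set also still conditions on death, itself a post-randomisation event, which is why death rates should be compared by arm.

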**Figure 2 F2:**
[figure not shown]
**Study design randomized controlled trial**.

### Outcomes

GPs of both study groups were invited to extract data of all patients that died during the observational period from the medical records: demographics, disease history, place of death, hospital admissions and out of hours consultations. Of each participating GP, demographic characteristics, practice characteristics and their interest in palliative care were collected (Table 3).

**Table 3 T3:** Baseline characteristics participating GPs^# ^(n = 133)

*Characteristics of general practitioners *	
Age - yr	48,2 ± 8,1

Gender male sex - no.(%)	81 (60, 9)

Working week fulltime - no. (%)	70 (52, 6)

Experience - no. (%)	

≤ 1 year	2 (1, 5)

2 - 5 years	14 (10, 5)

6 - 10 years	21 (15, 8)

≥ 10 years	94 (70, 7)

Missing	2 (1, 5)

Interest in palliative care*	8, 14 ± 1, 12

Missing	3

Estimation of own capability**	6, 83 ± 0, 92

Missing	3

*Characteristics of practice *	

Practice form - no. (%)	

Single-handed	28 (21, 1)

Dual	53 (39, 8)

Group and health centres	52 (39, 1)

Missing	0

Degree of urbanisation - no. (%)	

Very	46 (34, 6)

Moderate	28 (21, 1)

Less	41 (30, 8)

No	18 (13, 5)

Missing	0

Size of practice Fte-average practice^+^	1728 ± 409

Missing	1

*Palliative care*	

Palliative patients/y - no. (%)	

≤ 2 patients	10 (7, 5)

3 - 5 patients	72 (54, 1)

5 - 9 patients	43 (32, 3)

≥ 10 patients	6 (4, 5)

Missing	2 (1, 5)

Use of consultant palliative care - no. (%)	

Yes	105 (78, 9)

No	25 (18, 8)

Missing	3 (2, 3)

^#^Plus-minus values are means ± SD

^+ ^Size of practice = fulltime-equivalent/average practice (= 2350 patients)

*Interest in palliative care, visual analogue scale, rang 0, indicating no interest, to 10 very much interest.

** Estimation of own capability, visual analogue scale, rang 0, indicating not capable, to 10 very much capable.

### Data management and plan of statistical analysis

All data were entered in a database and analysed with SPSS 16.0. In both study groups, all patients who died during the inclusion and observation period of the study of a non-acute death, were included in the retrospective analysis. Intervention and control group will be compared on the main outcomes (place of death, number of transitions and out of hours contact, amount of identified patients). Recruitment rates and drop-out rates will be calculated. In case denominators prove to be significantly correlated with the outcome of the main study question, an Anova will be performed to identify potential related or independent factors. Multilevel analysis will be performed.

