## Methods/Design

### Study design

We performed a two-armed randomized controlled trial.

We studied the following hypothesis: H_0_: training GPs in early identification of palliative care patients and proactive care planning will not increase the percentage of patients that die at home, will not reduce the amount of hospital admissions and will not reduce the number of contacts with the out of hours primary care service. This hypothesis will be rejected if the training has a significant positive effect on these aspects of care.

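### The one stated covariate rule selects factors by significance against the outcome, through an ANOVA that suits neither home death nor counts, and does not assure the stratification factors a place

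*Protocol article*

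**What the plan says.** Under the heading on data management and statistical analysis, the protocol article compares the arms on "place of death, number of transitions and out of hours contact, amount of identified patients". It then gives its only rule on other factors: "In case denominators prove to be significantly correlated with the outcome of the main study question, an Anova will be performed". The stated purpose is "to identify potential related or independent factors". The word used for the candidate variables appears to stand for determinants. No candidate list is given. The section closes with "Multilevel analysis will be performed"; the levels, the link function and the fixed effects are not stated.

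The hypothesis under Study design fixes the type of outcome: training "will not increase the percentage of patients that die at home, will not reduce the amount of hospital admissions", and the third element is out-of-hours contacts. That is one binary outcome and two counts.

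Under Participants, GPs were "stratified for degree of urbanization and working hours (part-time or full-time") before random assignment, and "those GPs working together in the same practice were placed in the same study group". Table 3 records both stratification factors, as working week and degree of urbanisation.

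**The concern.** Three features of the rule are weak.

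- **Selection uses the outcome data.** A factor qualifies because it correlates significantly with the outcome in this trial, not because it was named beforehand. If the factors that qualify go into the treatment model, the adjusted effect, and for home death the conditional odds ratio itself, depends on which ones happened to pass. The rule speaks of one outcome, while the same section lists four, so different factors could be picked for each.
- **ANOVA does not match the data.** It models a mean on a linear scale with independent residuals. It gives neither an odds ratio for home death nor a rate ratio for contacts or admissions, and in its ordinary form it ignores that patients share GPs and practices.
- **The design factors are not secured.** Significance is the only criterion given. A stratification factor that fails the screen has no stated route into the model, although the randomisation was built on it.

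At stake are the reproducibility and interpretation of the adjusted estimates, and some precision.

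**Working it through.** **Candidate factors.** The article gives no list, so Table 3 serves as the plausible set. It contains, for the GP: age, gender, working week, experience, interest in palliative care and estimate of own capability (6). For the practice: practice form, urbanisation and size (3). For palliative care: palliative patients per year and use of a consultant (2). Total: 6 + 3 + 2 = 11.

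**Chance of at least one spurious selection.** Assume that none of the m factors is related to the outcome, that the tests are independent, and that each is done at 5%. The article does not state the threshold of the screen; 5% is borrowed from the alpha in the power calculation.

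P = 1 − (1 − 0.05)^m

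- m = 5: 1 − 0.95^5 = 0.23
- m = 10: 1 − 0.95^10 = 0.40
- m = 11: 1 − 0.95^11 = 0.43
- m = 12: 1 − 0.95^12 = 0.46

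The 11 factors are not truly independent (age and experience go together), so 43% is an order of magnitude. Ordinary patient-level tests that ignore clustering would push it up for factors that vary only between practices. No single design effect can be applied to all 11, though. Table 3 puts 53 + 52 = 105 of 133 GPs (79%) in dual or group practices, where partners can differ in age, gender, working week, experience, interest and self-rated capability. The article gives neither an intracluster correlation nor the number of patients per practice, so no clustered figure is offered.

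**Does this carry over to the comparison of arms?** Two checks under assumed values say that it need not.

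1. A plain two-group test (ANOVA with two groups) on 96 independent patients per arm, 20,000 simulated trials: type I error 5.2% for a binary outcome with probability 0.5, and 4.7% to 4.9% for negative binomial counts with mean 1 to 2 and dispersion 0.5 to 1. Non-normality alone does little harm to the error rate of a simple comparison. This check does not cover clustering.
2. Clustered data with 72 practices, 3 or 9 patients each, an intracluster correlation of 0.10 and a skewed outcome; 11 null factors screened at patient level without regard to clustering, then a comparison of arms that respects the clusters, 8,000 runs for each setting. At least one null factor was selected in more than half of the runs, yet the type I error for the arm effect was 4.6% to 4.9%.

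The reason is that the arm is randomised and the screen looks at the relation of factors to the outcome, not at the arm estimate.

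**Stratification factors.** Set side by side, the Participants section balances the arms on urbanisation and working hours, and the analysis section admits factors by significance. Where a balanced factor predicts the outcome and is left out, its variation stays in the error term. The usual result is a standard error that is too large, which is a loss of precision and not a false-positive risk.

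**The case against.** The strongest reply is that the ANOVA is not the treatment analysis. It is described as a step to find factors, and a multilevel analysis comes after it. That analysis acknowledges clustering and may well be logistic or count-based; nor does the article say outright that the selected factors enter it. All of this stands, and it limits the point to how covariates are chosen.

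A reader might infer more than the text supports in four ways.

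- *The trial will not adjust for the stratification factors.* The article neither names nor excludes them, and a covariate list is commonly left to a fuller document. What can be said is that the one stated rule does not guarantee them.
- *The p-value for the arm effect will be too small.* The 43% is the chance of picking a null baseline factor. The checks above show no inflation for a randomised arm analysed with regard to clusters.
- *Practices are ignored in favour of a model with GP as the only level.* No level is named, so no such model is stated.
- *The counts are skewed.* This is plausible, but the article gives no mean, standard deviation or distribution.

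What the reply does not remove is that the rule is stated. Condensation excuses what an article omits; it does not make a significance screen followed by ANOVA a sound way to choose covariates for binary and count outcomes.

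**Conclusion.** The point holds as a fault in the covariate rule, of moderate weight. Selection depends on the outcome data, and the named method fits neither home death nor the counts. With 11 candidates, at least one spurious factor would be expected in about 43% of trials, assuming independent null factors tested at 5% (23% to 46% for 5 to 12 candidates). That this alters the adjusted effect rests on the likely, but not explicit, reading that selected factors enter the multilevel model. The stratification factors have no assured place, with a possible loss of precision that cannot be sized from the article. The documents do not support a claim that the comparison of arms is invalid or that its error rate is inflated.

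**What to change.** Drop the significance screen and the ANOVA as the basis for choosing covariates. Specify the multilevel analysis already announced as:

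- a logistic model for death at home;
- a Poisson or negative binomial model for admissions or transitions and for out-of-hours contacts;
- a random effect for practice, with GP within practice if it can be estimated;
- prespecified fixed effects for arm, urbanisation and working hours, with disease group (CHF, COPD, cancer) as an option.

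Report the effects with 95% intervals. Label any further look at GP or practice factors as exploratory and keep it out of the model for the main comparison.

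Both stratification factors are in Table 3, and the outcomes and disease history are already extracted from the records. The cost is a change of wording and a little more modelling work.
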